## Methods

### Trial design

The Journaling App for Youth (JAY) study is designed as an interventional randomized controlled trial (RCT). It will include two parallel treatment arms: (1) cognitive-behavioural therapy (CBT) employing the Journaling App for Youth (CBT + JAY) or (2) cognitive-behavioural therapy employing traditional paper-and-pencil methods (CBT).

Figure 1 presents the trial design for the JAY study. Patients and their caregivers will be contacted by telephone for a preliminary screening, followed by an in-person screening and information session. Upon agreeing to participate, patients and caregivers will complete the first online questionnaires (T0). Subsequently, diagnostic sessions and sessions to introduce the patient to their therapist will be conducted.

**Fig. 1 Fig1:**
[figure not shown]
Study design of the JAY trial

Following these sessions, patients will be randomly allocated to one of the two treatment arms. After randomization, a baseline phase will take place, followed by the T1 assessment. In the subsequent treatment phase, patients in both groups will receive state-of-the-art CBT. In the treatment group (CBT + JAY), homework and assessments will be conducted through the JAY app, while in the active control group (CBT), equivalent tasks will be completed on paper. Each treatment phase will consist of eight sessions with the patient and up to four sessions with a caregiver. The first treatment phase will be followed by the T2 assessment. The final main assessment (T3) will take place after the second treatment phase. Depending on the clinical significance of remaining internalizing symptoms, patients will then either continue with a third treatment phase, which will be followed by the T4 assessment, or the intervention will be stopped and they will proceed to a first follow-up assessment after 8 weeks (T4). A subsequent follow-up evaluation (T5) for all patients will be scheduled 6 months after T4.

## Participants, interventions, and outcomes

### Study setting

The JAY trial will be a single-center study located at the Center for Child and Adolescent Cognitive Behavior Therapy (CEKIP), Faculty of Medicine and University Hospital Cologne, University of Cologne.

### Eligibility criteria

Eligible participants will meet the following criteria: (1) adolescents aged between 13;0 and 17;11 years at T1; (2) diagnosed with one of the specified clinical conditions according to the 10th International Statistical Classification of Diseases and Related Health Problems (ICD-10) [79], including depressive episode (F32.0, F32.1, F32.8, F32.9), anxiety disorders (F40.00, F40.01, F40.1, F40.8, F41.0, F41.1, F41.2), emotional disorder with onset specific to childhood (F93.0, F93.2), and adjustment disorder (F43.2), as assessed by a clinician using a structured clinical interview (DISYPS-ILF INTERNAL) [72]; (3) self-reported internalizing symptoms with a clinically relevant score (*T* value ≥ 60) on the Internalizing scale of the YSR/11-18R [69]; and (4) willingness and ability to participate in the intervention, including sufficient German-language skills and smartphone competences demonstrated by the patient.

Patients will be excluded if any of the following exclusion criteria are met: (1) presence of autism spectrum disorder (F84) or another severe comorbid disorder identified as clinically predominant; (2) adolescent’s intelligence level below average (intelligence quotient (IQ) < 80), determined using a standard intelligence test (German version of the Culture Fair Intelligence Test (CFT 20-R) [80]); (3) critical escalations of symptoms indicative of the need for inpatient treatment; (4) concurrent participation in additional outpatient treatment; (5) indication for initiating new pharmacotherapy or adjusting the dosage of existing pharmacotherapy at the time of the intervention.

### Consent

Informed consent will be obtained from patients and caregivers in written and verbal form prior to screening. For detailed information, please refer to Additional file 2: Model of written informed consent. Participants will have the opportunity to address any questions regarding the study with research staff members. Participation in the study requires assent and informed consent from both the patient and their caregivers. Data entry and processing will take place upon receipt of signed informed consent.

### Interventions

#### Explanation for the choice of comparators

The choice of an active control group rather than a placebo or no-treatment control group ensures that both groups will receive a recognised and effective form of treatment. This design will allow us to assess the added value of the app, if any, beyond the established benefits of CBT and therapy homework, thereby providing a meaningful comparison that can inform future clinical practice.

#### Intervention description

In the randomized control trial, each participant will receive cognitive behavioral therapy conforming to German clinical guidelines and based on international evidence-based treatment manuals (e.g., the SELBST program [81], THAZ—Social Anxiety [82], CBT for Depression in Childhood and Adolescence [83]). Participants will undergo 16 to 24 weekly therapy sessions, and up to 12 optional caregiver sessions will be provided (a maximum of four per treatment phase).

A personalized treatment plan will be created for each patient. Common elements of treatment include establishing rapport and motivation, resource activation, developing a mutual understanding of the disorder and its causes, psychoeducation, situational analysis, and setting treatment goals.

For the treatment of depressive symptoms, tailored interventions may include resource activation for low self-esteem, promoting activities for patients lacking positive experiences, problem-solving training for inadequate conflict resolution, cognitive restructuring for dysfunctional thought patterns, third-wave techniques for managing ruminative thoughts, and self-reinforcement for insufficient self-care.

Anxiety treatment may involve cognitive restructuring for dysfunctional thoughts, graduated exposure therapy combined with positive reinforcement to address avoidance behaviours, and competence training for lacking skills (such as social skills).

At the conclusion of each treatment, there will be an evaluation, relapse prevention strategies, and emotional detachment from the therapist.

The study therapies are conducted by child and adolescent therapists in training. Therapists need to be familiar with the app’s features and comfortable in incorporating the app into the therapy sessions. Otherwise, implementation of and fidelity to the intervention might be threatened. To limit this risk, therapists will receive a comprehensive introductory session to the app as well as ongoing support on how to integrate it into their therapy sessions effectively. The study staff will deliver this introductory session and offer continuous technical assistance. The supervisor will offer guidance to therapists on the effective integration of the app into therapy sessions. Additionally, a comprehensive user manual will be provided [67].

#### JAY smartphone app

During the CBT treatment, adolescents in the experimental group will use the JAY app [67] (see Fig. 2), which is designed for adolescents aged between 13 and 17 years and can be used in the treatment of mental disorders, e.g., anxiety and depressive disorders, conduct disorder, attention-deficit/hyperactivity disorder, and obsessive-compulsive disorder. The current study focuses on patients diagnosed with at least one of the two internalizing disorders anxiety and depressive disorders. The JAY app can be combined with a variety of CBT manuals and is designed to facilitate the implementation of therapeutic homework and the transfer of coping strategies into patients’ daily lives. It can also be used for diagnostic and progress monitoring purposes. The app can be customized with regard to design (according to the patient’s wishes), difficulty of tasks (depending on therapy progress), and individual questions defined by the therapist. The different functions of the app are described in greater detail below [67].

**Fig. 2 Fig2:**
[figure not shown]
Main menu of the JAY app (version 1.1.0)

The *design function* allows patients to individualize the app’s interface, including colours, backgrounds, and an avatar that interacts with the patient. This is supposed to increase therapy motivation.

The *psychoeducation function* supports youth-friendly psychoeducation involving explanatory graphics. These illustrate the causes of problem behaviour (“This is how it may be”), introduce CBT interventions, and allow an outlook for improvement (“This is how it may become”).

The *momentary assessment function* (see Fig. 3) assesses the intensity of 18 affective and mental states (e.g., happy, afraid, relaxed, sad), 16 of which will be used in the current study. This is a tool for self-observation of mood in real time, which can yield data without retrospective biases. The collected data can be valuable for clinicians in terms of diagnosing mood disorders or tracking the effectiveness of treatment over time. Moreover, the function can make individual queries, allowing for specific questions tailored to the patient’s situation. Queries will only occur at predetermined times upon which the patient and therapist have agreed, and cannot otherwise be triggered. This ensures that mood data are collected consistently and at relevant intervals. Once alerted, the user has a time window of 1 h to complete the mood assessment, thus providing flexibility while still capturing data within a relevant time frame.

**Fig. 3 Fig3:**
[figure not shown]
Momentary assessment function of the JAY app (version 1.1.0)

The *diary function* (see Fig. 4) can be used to report on difficult situations that patients encounter in their everyday lives, including cognition, behaviour, and consequences of behaviour, among other things. Diary entries can be made during or after the situation, allowing for a better transfer to therapy. The app specifically prompts the patient to analyze the situation, guiding the process. This function is supposed to support the training of the ability to reflect. First, questions about difficult situations are asked. If the patient indicates that a difficult situation has not occurred, a positive experience can be reported instead. When activated, the diary function is accessible to patients at any time in the home menu. The content and structure of the prompts can be modified in terms of disorder-specific questions and with respect to the complexity of the questions. For each question that requires input, the patient can choose between a text entry and a video recording.

**Fig. 4 Fig4:**
[figure not shown]
Diary function of the JAY app (version 1.1.0)

The *reminder function* prompts the patient to start his/her therapy homework that has been individually agreed upon. A first notification is set up as reminder to accept the challenge, and a second notification prompts the patient to document whether the challenge was accepted, how it went, or what caused it to fail.

The *problem-solving function* aims to help patients develop problem-solving skills by acting as their own “director” in challenging situations. A problematic situation can be defined in the app. The patient is then confronted with the situation and asked for a strategy to solve the problem. A specific action goal can be set, e.g., to calm oneself down.

The *coping skills function* provides patients with a structured and accessible way to learn and apply various coping strategies for managing stress, emotions, and challenging situations. Those coping strategies are presented within four overarching categories: (1) thought-related skills, (2) relaxation, action, and sensory-related skills, (3) problem-solving skills, and (4) reward and helping skills. Various subcategories are available, as well as the option to record the use of skills in a skills diary. Once activated in the settings, this function can be accessed autonomously by the patients. Individual skills can be added in order to personalize the experience.

The *reinforcement function* serves as a motivational system that rewards adolescents for actively engaging with the app’s features. By engaging with the various functions, patients can earn coins. These can be redeemed in the app’s virtual store for an app-internal game (Blocks or Snake) or for three individually determined wishes with different values.

#### Modifications

The study participation of single subjects will be terminated early, and subjects will be defined as dropouts, if at least one of the following conditions is met: (i) at least one parent/caregiver withdraws the informed consent, (ii) the patient withdraws the informed consent, (iii) the patient requires inpatient treatment or another kind of outpatient treatment in order to safeguard his or her well-being, which may be affected by continued trial participation.

The principal investigators may decide to terminate the entire trial if less than 50% of the planned sample size can be recruited despite additional recruitment strategies.

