#### Concomitant care

During the trial, concurrent psychotherapy will be prohibited for participants. This is because receiving additional psychotherapy would not only conflict with the study’s treatment protocol but is also contrary to clinical recommendations. If a participant begins concurrent psychotherapy during the trial, this will result in their dropout from the study in order to maintain the integrity of the trial’s outcomes and ensure consistency in the treatment being evaluated.

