### Retention

To promote participant retention and ensure complete follow-up, patients will receive email reminders to complete the follow-up questionnaire. If there is no response to the email, a reminder telephone call will be made. For participants who discontinue or deviate from the intervention protocols, any available outcome data collected up to that point will still be used in the analysis in order to maintain the integrity of the study results, as long as patient or parent consent is not withdrawn.

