## Statistical methods

### Statistical methods for primary and secondary outcomes

#### Analyses of primary endpoint

The primary analysis set adheres to the intention-to-treat (ITT) principle, comprising all patients randomised with a valid baseline assessment. Additionally, per-protocol analyses will involve all patients who attend at least 50% of the planned treatment sessions and provide a valid follow-up. The primary endpoint is the overall THA score across the intervention (sessions 1–16). Subsequent analyses assess changes in phase 1 (sessions 1–8 from T1 to T2) and changes in phase 2 (sessions 9–16, between T2 and T3). A mixed model repeated measures multivariate analysis of variance will be conducted, with the between-subjects factor Group (smartphone-augmented vs. traditional), the within-subjects factor Time (T2, T3), and the interaction effect of Group × Time.

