### Missing data

It is important to minimize treatment discontinuation among patients and ensure that all patients are followed up and documented after treatment discontinuation in order to collect the data according to the intention-to-treat (ITT) principle. Multiple imputation approaches will be employed to evaluate the potential impact of up to 20% attrition, considering proxy measures and assuming specific patterns of missingness not at random. These details will be documented in a statistical analysis plan. Additionally, supporting evidence will be provided by analyzing subjects who are essentially observed and treated per protocol.

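### Patients who need other care or start other psychotherapy leave the study with consent intact, although the missing-data section wants everyone followed after treatment stops

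*Protocol article*

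**What the plan says.** Four sections of the Protocol article govern what happens when a patient stops, and a fifth defines the analysis set.

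- **Modifications:** "The study participation of single subjects will be terminated early, and subjects will be defined as dropouts" if any of three conditions is met. Two are withdrawal of consent, by a caregiver or by the patient. The third is that "the patient requires inpatient treatment or another kind of outpatient treatment in order to safeguard his or her well-being".
- **Concomitant care:** "If a participant begins concurrent psychotherapy during the trial, this will result in their dropout from the study".
- **Retention:** for participants who discontinue or deviate from the intervention, "any available outcome data collected up to that point will still be used in the analysis", provided consent has not been withdrawn.
- **Missing data:** the team should "ensure that all patients are followed up and documented after treatment discontinuation in order to collect the data according to the intention-to-treat (ITT) principle". The same section adds: "Multiple imputation approaches will be employed to evaluate the potential impact of up to 20% attrition". This includes patterns missing not at random, with details left to the statistical analysis plan.
- **Analyses of primary endpoint:** "The primary analysis set adheres to the intention-to-treat (ITT) principle, comprising all patients randomised with a valid baseline assessment".

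The Participant timeline section also expects every family to complete the T5 survey.

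**The concern.** The third condition under Modifications and the rule under Concomitant care apply to patients who have not withdrawn consent. Both take the patient out of the study. The Missing data section treats stopping treatment as something after which observation continues. No section separates the two events, so staff reading the protocol cannot tell whether such a patient should receive the next questionnaire.

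What is at stake is the symptom comparison. Needing other care, or looking for other therapy, is plausibly linked to how the patient is doing. If observation stops at that moment, the missing values are unlikely to resemble those of patients who stay. A statistical analysis plan can specify how to impute them, but it cannot recover questionnaires that were never sent.

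**Working it through.** This is a question of consistency, so the check sets the sections side by side for each way a patient can stop.

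1. **Consent withdrawn by patient or caregiver.** Modifications ends participation. Follow-up cannot be demanded. No conflict.
2. **Study therapy stopped, consent stands, no other care.** This is not a condition under Modifications, so the follow-up required under Missing data can operate. No conflict.
3. **Inpatient or other outpatient care needed, consent stands.** Modifications ends participation; Missing data requires follow-up. Conflict.
4. **Other psychotherapy begun, consent stands.** Concomitant care makes the patient a dropout from the study; Missing data requires follow-up. Conflict.

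Retention does not settle cases 3 and 4. It promises that data already collected will be kept and used, and makes no provision for collecting more after discontinuation.

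**Which outcomes are affected** (Primary outcome and Secondary outcomes sections):

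- The primary score multiplies the share of requested homework entries completed by their rated quality, over sessions 1–16. It needs ongoing study homework, so later questionnaires cannot supply it.
- The Internalizing scales of the YSR and CBCL are due at every time point. The anxiety and depression checklists, the comorbid-symptom scales, quality of life, self-worth and emotion regulation are due at T3. These are questionnaire outcomes that could still be collected.
- The clinician interview at T3 needs visits, and the individual problem list is filled in at therapy sessions. An online survey does not replace either.

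**Whether follow-up is feasible.** Patient and caregiver questionnaires are already completed online (Data collection methods). E-mail and telephone reminders for the follow-up questionnaire exist (Retention). Responders already complete T4 and T5 after their therapy has ended (Trial design, Participant timeline). Assessment outside treatment is therefore routine in this trial.

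**Scale.** Inputs: 70 patients, 35 per arm (Sample size); up to 20% attrition (Missing data).

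- 0.20 × 70 = 14 patients.
- If split evenly, 0.20 × 35 = 7 per arm, leaving 35 − 7 = 28 per arm.

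The 14 covers attrition from every cause. The document does not say how many would come from cases 3 and 4.

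**The case against.** Several counter-arguments have force, and each limits the point.

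- **The analysis can still be run.** A reader might infer that the intention-to-treat analysis cannot be delivered. The documents do not support that. The set is all randomised patients with a valid baseline, the exit rules remove nobody from it, and multiple imputation with not-at-random scenarios is planned. What is missing is the observed data after discontinuation that the Missing data section itself asks for.
- **The primary endpoint is largely out of reach of the fix.** This stands. The point concerns secondary outcomes.
- **Retention does not say that only earlier data count.** Correct: its sentence is a promise not to discard data. But nothing elsewhere commits the team to collecting later data from patients already declared dropouts.
- **Treatment discontinuation and study termination are different events.** This holds for case 2 above and confines the conflict to cases 3 and 4.
- **Unequal loss between arms is not shown.** The Discussion reports that pilot patients using the app felt less supported by their therapist and that adherence to therapy and research protocol fell. It also reports the response: three therapist sessions placed before the baseline phase. It describes no control arm and no pilot patient moving to other care. Unequal loss is a possibility only.
- **A bias figure is tempting.** A reader might multiply a difference in dropout proportion by the outcome gap between leavers and stayers. Assuming a 10 to 20 point difference and leavers 1 SD worse gives 0.10 × 1 = 0.10 SD to 0.20 × 1 = 0.20 SD, which is 20% to 40% of an assumed 0.5 SD effect. All of these inputs are assumed. The formula describes an unadjusted comparison of completers, whereas the plan names mixed models or generalized estimating equations, plus imputation. With 14 leavers in total, a 20-point difference means 30% against 10%, or 10.5 against 3.5 patients: a 3:1 split. Attributing all of that to the two exit rules has no basis in the document.

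**Conclusion.** The conflict is real but narrow. The third condition under Modifications and the rule under Concomitant care end participation for patients who still consent, while the Missing data section requires follow-up after treatment stops. If the exit rules are followed, the remaining questionnaire outcomes from T2 to T5 are lost for these patients, and the intention-to-treat comparison of those outcomes depends on imputation assumptions that cannot be checked.

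The primary homework score is largely unaffected by the remedy. The only scale the document offers is its 20% planning value for all attrition, 14 of 70 patients; the size and direction of any bias cannot be derived from it. That leaving is related to outcome is a plausible assumption, not something the document demonstrates. The conflict should be resolved in the protocol, because data not collected cannot be restored at the analysis stage.

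**What to change.** Reconcile Modifications, Concomitant care and Retention with Missing data by separating two events: discontinuation of study treatment, and withdrawal from data collection. Leave the clinical rules for ending study treatment as they are.

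- Unless consent is withdrawn, or further questionnaires are judged to affect the patient's well-being, keep sending the existing online patient and caregiver questionnaires at the remaining time points.
- Because T2 to T4 are tied to therapy sessions, state when they fall for a patient who no longer has sessions.
- Record the date and reason of discontinuation.
- Include these data in the intention-to-treat analysis of the symptom outcomes.
- Handle consent withdrawal and ordinary non-response by the planned multiple imputation.

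The cost is revised wording in three sections and a little more follow-up work for staff. The online survey and the reminder procedure already exist.
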